**Methods:**

A total of 148 patients with CAD and/or VHD after surgical intervention and concomitant psychological distress (defined as HADS anxiety (A) or depression (D) score ≥8) will be randomized to either usual out-patient cardiac rehabilitation (CR) comprising an 8-week multidisciplinary programme or usual care supplemented by five group-based cognitive therapy sessions performed by trained CR nurses. A structured, standardized treatment manual will be used. Patients will be randomized 1:1 at three different sites. Additionally, a non-randomized sub-group of 40 matched patients without signs of psychological distress will be followed to investigate spontaneous variation in HADS. The primary outcome is Hospital Anxiety and Depression Score (HADS). Secondary outcomes are adherence to cardiac rehabilitation (CR), health-related quality of life measured by HeartQoL, time to return to work, adherence to lifestyle interventions and cardiovascular readmissions. Patients are followed up for 12 months.

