### Participants

The trial is a multi-centre trial planned to include 188 patients from three departments of cardiology. The main trial includes 148 randomized patients. We will also include a non-randomized subgroup of 40 matched patients (relative to inclusion and exclusion criteria) without signs of psychological distress to investigate spontaneous variation in HADS scores over time.

Inclusion criteria are:
Referred to CR and accepting CRPatients with newly diagnosed CAD and/ or surgically treated VHDHADS score > 8 for HADS-A and/or HADS-DAge < 65 yearsAble to speak and understand Danish

Exclusion criteria are:
EF < 35%Other serious comorbidity expected to have a serious impact on life expectancyKnown abuse of alcohol or euphoric drugsKnown more serious psychopathology such as schizophrenia, bipolar disorder, severe personality disorder and treatment with psychoactive drugs

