**Risk factors**									
Hypertension	x								
Dyslipidaemia	x								
Diabetes mellitus	x						x	x	
Family history	x								
Smoking	x						x	x	
Physical activity	x						x	x	
Rehabilitation received							x	x	

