### Secondary outcomes

Secondary outcomes are adherence to CR defined as > 80% participation in planned training sessions (used as a secondary outcome under the hypothesis that participation in group-based therapy will improve CR adherence), health-related QoL measured by the questionnaire HeartQoL, return to work, marital status, adherence to medication and lifestyle interventions for CVD risk factor goals defined as four separate outcomes: HbA1c < 48, BP < 135/85 mmHg, BMI < 30 and LDL < 1.4 mmol/l, physical activity (days per week with ≥ 30 min of moderate physical activity) and cardiovascular readmissions at 12 months.

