### Sample size and power calculation

The primary outcome is a change in HADS score at 3 months. A clinically relevant difference between groups would be a reduction in the total sum score of 2. In a previous study [36], the change within each group was normally distributed with a standard deviation (SD) of 2.5. We have here used a more conservative estimate with an SD of 4. Under these assumptions with a risk of type 1 error of 0.05 and a power of 0.8, 64 patients should be included in each group. Due to the risk of dropout of patients included in this type of trial, the total number of patients included is increased by 15% to 148 patients

STATA II, the Ralloc programme is used for randomization, permuting random block sizes of 2,4 and 6.

To assess the spontaneous variation in HADS scores over time, we will investigate a non-randomized group of 40 matched patients (relative to inclusion and exclusion criteria) without signs of psychological distress (i.e. HADS A < 8 and HADS D < 8) at first measurement with re-evaluation after 3 and 6 months. With 64 patients in the usual care arm and assuming a SD of 4 as above, we will have 80% power to detect a difference in change in HADS score (delta HADS) of 2.3 or more between these two groups.

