### Statistical analysis

The primary analysis will be a comparison of the intervention and control group in mixed-models linear regression with robust standard errors with 3-month values as outcome, and baseline and 6 months values will be used as adjustment variables. Analyses will also be adjusted for the centre and tested for treatment-centre interaction. For the analysis of the secondary outcomes return to work (yes/no), HbA1c< 48, BP< 135/85 mmHg, BMI< 30, LDL< 1.4 mmol/l and physical activity, we will also apply repeated measures regression. For adherence to CR (> 80%), we will compare groups by logistic regression adjusting for the centre. For the outcome of re-admission at 12 months, we will compare outcomes across groups with Kaplan-Meier curves and time-to-event analyses (Cox regression) adjusting for age, left ventricular ejection fraction, co-morbidities and risk factors as described above. A two-sided P < 0.05 will be considered statistically significant, and all primary outcome analyses will be performed without knowledge of group allocation.

We will compare the primary outcome in intervention and control groups with the spontaneous variation in the non-distressed subgroup of 40 participants by separate mixed-models linear regression adjusting for baseline values and centre.

The primary reported analyses will be carried out as a modified intention-to-treat as participants with missing data on a primary or secondary outcome will be excluded from the corresponding analyses. The analysis is supplemented with per-protocol analyses defined by participation in ≥ 4 of the 5 group-based sessions. Missing information on other co-variates will be permuted if there is < 20% missing data for the co-variate in question.

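### The readmission Cox model is written with 12 covariates plus treatment, too many for the events 148 patients are likely to supply, so its hazard ratio will be unstable and imprecise

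*Protocol article*

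**What the plan says.** The Statistical analysis section compares 12-month readmission between groups by Kaplan-Meier curves and by Cox regression, the latter "adjusting for age, left ventricular ejection fraction, co-morbidities and risk factors as described above". It gives no rule for reducing the list and does not say at which visit the covariates are measured.

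The headings in Table 1 match that wording. The comorbidity block has four rows: history of heart disease, chronic obstructive pulmonary disease, kidney disease and depression. The risk-factor block has six rows with a baseline mark: hypertension, dyslipidaemia, diabetes, family history, smoking and physical activity. A seventh row, "Rehabilitation received", is marked only at 3 and 6 months. Diabetes, smoking and physical activity are marked at baseline and again at both follow-up visits.

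On size, the Participants section states: "The main trial includes 148 randomized patients". The sample size calculation concerns the HADS score alone. No readmission rate, event count or power is given for the Cox model.

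**The concern.** In a Cox model the information lies in the events, not in the patients. A list of this length, fixed in advance for a trial sized on a questionnaire score, is likely to leave very few events per estimated coefficient. The treatment log hazard ratio then becomes noisy, its model-based standard error tends to be too small, and a real effect tends to be exaggerated. Randomisation already balances baseline factors in expectation, so the list is not needed to remove confounding.

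The second issue is wording. CR adherence is a secondary outcome that the protocol expects the group therapy to improve. If the amount of rehabilitation received after allocation were used as a covariate, part of any treatment effect on readmission could be adjusted away.

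At stake is the hazard ratio for the main morbidity outcome in the secondary list. The Discussion names reduced morbidity as a hoped-for benefit.

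**Working it through.** **1. What the sample size covers.** The inputs are "A clinically relevant difference between groups would be a reduction in the total sum score of 2", an SD of 4, and "a risk of type 1 error of 0.05 and a power of 0.8, 64 patients should be included in each group". The normal approximation is n = 2 × SD² × (1.960 + 0.842)² / δ² = 2 × 16 × 7.85 / 4 = 62.8, so 63 per arm. The exact t-test needs 64 (power 0.801, against 0.795 with 63). Inflation gives 128 × 1.15 = 147.2, so 148. The stated figures reproduce, and readmission plays no part in them.

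**2. Number of parameters.** Age and ejection fraction (2) + comorbidities (4) + baseline risk factors (6) = 12 covariates. Treatment makes 13. Counting "Rehabilitation received" makes 14. If the general statement on centre adjustment also covers this model, three sites add two more, up to 16.

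**3. Events per parameter.** The readmission rate p is an assumption. Events = 148 × p.

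| Assumed p | Events | Per parameter (÷ 13) |
|---|---|---|
| 10% | 14.8 | 1.1 |
| 15% | 22.2 | 1.7 |
| 20% | 29.6 | 2.3 |
| 25% | 37.0 | 2.8 |
| 50% | 74.0 | 5.7 |

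Five events per parameter would need 65 events (65/148 = 44% readmitted). Ten would need 130 (88%).

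**4. Cost of the list when the covariates carry no information.** The simulation used 148 patients allocated 1:1, exponential event times censored at 12 months, three continuous and nine binary covariates (assumed prevalences 6-60%), no treatment effect, no covariate effects and 2,000 replicates. Any increase in SD here is pure cost.

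| Mean events | SD, 12 covariates | SD, treatment only | SD ratio | Mean SE / SD, 12 covariates | Type I, 12 covariates | Type I, treatment only |
|---|---|---|---|---|---|---|
| 11.9 | 0.809 | 0.643 | 1.26 | 0.87 | 4.5% | 2.6% |
| 17.6 | 0.608 | 0.526 | 1.16 | 0.89 | 6.1% | 4.4% |
| 29.5 | 0.438 | 0.386 | 1.13 | 0.92 | 6.2% | 4.2% |
| 44.4 | 0.348 | 0.311 | 1.12 | 0.93 | 6.5% | 4.6% |

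The Monte Carlo error of each type I figure is about √(0.05 × 0.95 / 2000) = 0.5 points.

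**5. Against the model proposed below** (treatment, centre, age, ejection fraction), with no treatment effect, at about 15, 21 and 35 events. The 12-covariate SD is 14-24% larger. SE/SD is 0.84-0.91 against 0.91-0.98, so the reported SE falls 9-16% short of the true SD. Type I error is 6.3-6.8% against 4.4-5.9%. Another run with different assumed prevalences gave SD excesses of 22%, 14% and 9% at 17, 25 and 41 events.

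**6. With a true hazard ratio of 0.6** (log −0.511). At 16.4, 26.7 and 39.5 events the 12-covariate model gives mean log hazard ratios of −0.601, −0.572 and −0.560, which are 18%, 12% and 10% too large (for example 0.601/0.511 = 1.18). Treatment alone gives −0.513, −0.507 and −0.493.

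**The case against.** Prespecified covariate adjustment is legitimate in a randomised trial and can gain power. With a true hazard ratio of 0.6, the 12-covariate model did reject more often than treatment alone: 17.1% against 13.0% at 16.4 events, and 25.5% against 22.2% at 26.7. This stands in part. However, the mean estimate divided by its true SD is lower for the long model (0.601/0.715 = 0.84 against 0.513/0.573 = 0.90 at 16.4 events; 0.572/0.488 = 1.17 against 0.507/0.415 = 1.22 at 26.7). At least some of the extra rejections therefore come from understated standard errors.

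The readmission rate is also assumed. That is correct, but the conclusion does not hinge on it, because events per parameter stay below 6 at 50% readmitted.

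A reader might infer that the HbA1c, blood pressure, BMI and LDL targets enter the Cox model as risk factors. The documents do not support this. Secondary outcomes lists them as "CVD risk factor goals defined as four separate outcomes", and Statistical analysis handles them as outcomes by repeated measures regression.

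A reader might also infer that adjustment for post-randomisation variables is planned. That is not established. Trial procedure and randomization says that baseline data are collected before randomisation and points to Table 1, no time-varying covariates are mentioned, and rehabilitation received is not a risk factor in the ordinary sense. Baseline values are the natural reading. What stands is that the text does not say so, and that whether this row would enter is unclear.

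**Conclusion.** The point holds as one of instability and lost precision in a secondary analysis. As written, the model has at least 13 parameters for about 15-37 events at an assumed 10-25% readmission rate. The hazard ratio is then estimated with an SD about 14-24% larger than necessary, a standard error about 9-16% too small, and some exaggeration of a true effect.

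It would go too far to call the test invalid. Type I error rises only to about 6-7%, and in the simulations with 12 covariates the coverage of the 95% interval stayed at 93.1-94.7%. Nor should failure of the fit be stressed. Its frequency depends on how rare the binary covariates are: at most 1.7% of fits in one set of simulations, and up to 10% in another.

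The simulation figures rest on assumed covariate prevalences and effects, and the covariate count rests on reading the list against Table 1. The planned Kaplan-Meier curves give an unadjusted display in any case. The HADS analysis and the sample size are unaffected.

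**What to change.** Replace the adjustment clause with a sentence to this effect: the Cox model for 12-month readmission includes treatment, age and baseline left ventricular ejection fraction, is stratified by centre, and uses only values measured before randomisation. Drop the comorbidity and risk-factor list from this model.

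With centre as strata, three coefficients remain, so 14.8/3 = 4.9 to 37/3 = 12.3 events per parameter over the same assumed 10-25%. With centre as two indicator terms there are five coefficients, giving 3.0 to 7.4. Ejection fraction has no row in Table 1, but the exclusion criteria use it, so a baseline value should exist. It would help to add the row and to state the expected number of readmissions.

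The cost is one sentence, plus a small possible gain in power from other prognostic factors that is forgone. Enrolment was still open when the protocol was published, so the change could be made before any comparison of the groups. This is a cheap improvement, not a condition for the trial's main result.

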### Primary outcome

The primary outcome is mean (method of aggregation) change (metric) in psychological distress (domain) measured by HADS total score (specific measurement) from baseline to three months (time) in the intervention group compared with the usual care group. This outcome may be subject to ascertainment bias when blinding is not possible, e.g. social desirability bias causing participants to respond more favourably. We have attempted to limit this by administering the paper questionnaires to be filled in unsupervised. Furthermore, since both the intervention and the control group receive usual CR in the same cardiac settings, both groups may be subject to similar social desirability bias. At the 6-month follow-up, we anticipate that this bias will be reduced.

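### The primary HADS comparison is fixed as a complete-case analysis that sets aside usable 6-month scores and is open to bias of unknown size and direction if missingness relates to outcome differently by arm

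*Protocol article*

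**What the plan says.** All of the following is in the protocol article.

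- **Population (Statistical analysis).** "The primary reported analyses will be carried out as a modified intention-to-treat", which the same sentence explains: "participants with missing data on a primary or secondary outcome will be excluded from the corresponding analyses".
- **Model (Statistical analysis).** The primary analysis is a mixed-models linear regression "with 3-month values as outcome, and baseline and 6 months values will be used as adjustment variables", also adjusted for centre.
- **Other provisions (Statistical analysis).** Imputation is mentioned for covariates only: "Missing information on other co-variates will be permuted if there is < 20% missing data for the co-variate in question". The one supplementary analysis restricts the population further: "The analysis is supplemented with per-protocol analyses defined by participation in ≥ 4 of the 5 group-based sessions".
- **Expected loss (Sample size and power calculation).** The sample is enlarged by 15% to 148, with the reason given as "Due to the risk of dropout of patients included in this type of trial".
- **Blinding.** On the self-completed HADS, the Primary outcome section says "This outcome may be subject to ascertainment bias when blinding is not possible". Analysts are masked: "all primary outcome analyses will be performed without knowledge of group allocation".
- **Burden and follow-up.** Under CBT intervention, only the intervention arm has five 2-hour sessions with homework. Table 1 schedules HADS at baseline, 3 and 6 months in both arms.

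**The concern.** Having a 3-month HADS is a post-randomisation event. An analysis restricted to patients who have one compares subsets of the arms, and randomisation protects that comparison only if missingness is unrelated to outcome given the covariates, or related in the same way in both arms. Here the arms differ in burden and patients know their allocation, so a difference in who returns the questionnaire is plausible. Masking the analysts has no bearing on that.

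The rule also wastes information. HADS is collected at 6 months, and a mixed model with both visits as outcomes could use that score for a patient who missed the 3-month visit. As written, the 6-month score sits on the right-hand side of the model, so it cannot help such a patient. What happens to a patient who lacks only the 6-month score is not clear.

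At stake is the trial's headline result. The rule is stated for the primary reported analysis, so a later analysis plan could add to it but would have to contradict it to remove it.

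**Working it through.** **1. The plan's own figures.** Inputs from Sample size and power calculation: difference 2, SD 4, type 1 error 0.05 (two-sided, from Statistical analysis), power 0.8. The normal formula 2 × (1.96 + 0.84)² × 4² / 2² gives 63 per arm; the t-test version gives 63.8, so 64 as stated. Inflation: 64 × 1.15 = 73.6, so 74 per arm and 148 in total. The stated figures reproduce.

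**2. Precision after the expected loss.** 148 × 0.85 = 125.8, or 62.9 per arm. Power for a difference of 2 is then 0.80 (normal) or 0.79 (t-test). The allowance does its job for precision but does nothing for validity.

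**3. Bias of a complete-case comparison.** Let p be the share missing in an arm, and g the number of points by which the HADS change of non-completers is worse than that of completers in the same arm. The full-arm mean is (1 − p) × completer mean + p × (completer mean + g), so the completer mean looks better than the full-arm mean by p × g. The bias in favour of CBT is

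p(CBT) × g(CBT) − p(control) × g(control).

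The documents give neither p by arm nor g, so every row below is an assumption. It is an unadjusted comparison with 74 randomised per arm and SD 4; g should be read as the gap left after baseline HADS and centre are accounted for.

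| Missing, CBT / control | Gap g | Bias towards CBT | Share of the 2-point target | Nominal 5% error becomes |
|---|---|---|---|---|
| 15% / 15% | 2 to 4, both arms | 0 | 0 | 5% |
| 15% / 15% | 2 to 4, CBT only | 0.15×2 = 0.3 to 0.15×4 = 0.6 | 15 to 30% | 7.1 to 13.4% |
| 15% / 15% | 2 to 4, control only | −0.3 to −0.6 | 15 to 30%, against CBT | 7.1 to 13.4% |
| 20% / 10% | 2 to 4, both arms | 0.10×2 = 0.2 to 0.10×4 = 0.4 | 10 to 20% | 5.9 to 8.7% |

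**4. How much bias would matter.** With 62.9 per arm, SE = 4 × √(2/62.9) = 0.713 and 1.96 × SE = 1.40. An observed difference of exactly 2 therefore has a margin of 2 − 1.40 = 0.60 points. With 15% missing and the gap in the CBT arm only, that margin is used up at g = 0.60/0.15, about 4 points, which is one design SD.

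**5. What joint modelling recovers.** Take 15% missing in the CBT arm and g = 3, so the complete-case bias is 0.15 × 3 = 0.45.

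- If these patients miss both visits, they contribute nothing to the likelihood and the bias stays about 0.45.
- If they miss only the 3-month visit, assume the same 3-point gap at 6 months, equal SDs and a residual correlation of 0.6. The 6-month score then accounts for 0.6 × 3 = 1.8 of the 3 points, and the bias falls to 0.15 × 1.2 = 0.18.

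Joint modelling helps with intermittent missingness only, and even there it does not remove a not-at-random difference.

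**The case against.** The strongest reply is that nothing in the protocol shows differential loss. Exclusion depends on a missing score, not on missed sessions: a patient who stops CBT but returns the 3-month HADS stays in the primary analysis. Trial procedure and randomization describes flexible appointments, reminders and telephone contact, and the reason it gives for loss, working schedules, applies to both arms. Most of this stands. It lowers the probability of bias and leaves its direction open, but it does not justify discarding scores that were collected.

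A second reply is that the label is candid: the plan says modified and defines the modification in the same sentence. That is true; the concern is the rule, not its name.

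A third is that a mixed model is named, and that the secondary outcomes are said to use repeated-measures regression as well, which suggests that joint modelling of both visits may have been intended. It may have been. The text nevertheless names the 3-month value as the outcome and the 6-month value as an adjustment variable, and the exclusion rule follows.

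A reader might also infer that the rule mishandles two secondary outcomes, by treating patients who leave cardiac rehabilitation as missing for adherence and by excluding, not censoring, patients lost before 12 months. The documents do not support this. Someone who leaves rehabilitation has an observed participation below the threshold, and nothing says they are coded as missing. Kaplan-Meier and Cox methods censor by construction.

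**Conclusion.** The point holds for the primary HADS comparison, in conditional form. The protocol fixes a complete-case analysis where a better one is available from data already scheduled, and the result is exposed to bias if missingness relates to outcome differently by arm after adjustment for baseline and centre.

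Size and direction are unknown. The range of 0.3 to 0.6 points assumes 15% missing in each arm and a gap of 2 to 4 points in the CBT arm alone. Reversing the arms reverses the sign, and equal dropout with equal gaps gives zero. It would be tempting to conclude that the effect of CBT will be overstated, or that the trial will be underpowered. Neither follows: the first needs a one-sided dropout pattern that the documents do not show, and the second is answered by the 15% allowance.

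The absence of a sensitivity analysis from this article is not itself a fault, since it may be in an analysis plan that is not shown.

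**What to change.** Replace the exclusion rule for the primary outcome. Analyse randomised patients in their assigned arm with a likelihood-based repeated-measures model: 3- and 6-month HADS as outcomes, treatment by visit, baseline HADS and centre as covariates, and the 3-month treatment contrast as the primary estimate. Remove 6-month HADS from the adjustment set. Anyone with at least one follow-up HADS then contributes under missing-at-random.

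Add, if the analysis plan does not already have it, a delta-adjusted sensitivity analysis covering patients with missing scores, including those with no follow-up HADS. Shift the missing values in each arm separately over a stated range, for example 0 to 4 points (up to one design SD), and report where the conclusion changes. This step is needed because the model alone does not remove not-at-random bias. Report missing HADS by arm and visit.

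The cost is revised wording and a little more programming, with no new data. The price is reliance on a missing-at-random assumption in the primary analysis, which the sensitivity analysis then tests. The adherence and readmission analyses need no change on this account.
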